## 4 Study Setting

KPSC is one of the largest not-for-profit health plans and integrated health care systems in the U.S., providing an ideal environment for population-based research. KPSC's population includes more than 4.5 million members, of which 702,136 adults are aged  $\geq 65$  years and 341,464 are between 12 and 17 years old (Table 1). The diverse demographic makeup, including 260 different ethnicities and more than 150 different languages, closely mirrors the Southern California population. Compared to the racial/ethnic distribution of the U.S. population, KPSC membership is composed of twice as many individuals of Asian/Pacific Island descent and three times as many Hispanic individuals.[12]

KPSC facilities include hospitals and medical offices, all linked by an information infrastructure that supports both clinical practice and business needs. Health information from this infrastructure can be leveraged for research purposes. More than 90 percent of members remain in the health plan after one year; more than three-quarters remain after three years. The large, diverse, and stable population permits the rapid accrual of a representative sample size and offers the ability to evaluate long-term implications of immunization.

Kaiser Permanente HealthConnect® is the largest and most advanced civilian electronic health record system available in the U.S. In addition to supporting patient care, this robust system facilitates research, providing access to electronic health records (EHR) for the research team. The medical record number serves as a unique identifier linking all medical encounters for each member. Care received in the outpatient, inpatient, and emergency settings is documented in the EHR and captured in research databases. Care received outside the KPSC system is captured through claims. Details of care are available at the fingertips of researchers in near real time.

Our EHR include a variety of data that can be used for research:

**Membership:** Includes demographic information such as sex, date of birth, and race/ethnicity.

**Diagnosis:** Includes International Classification of Diseases, 10th revision (ICD-10) codes.

**Procedure:** Includes ICD-10, Current Procedural Terminology (CPT), and Systematized Nomenclature of Medicine (SNOMED) codes.

**Immunization:** Includes vaccine name, date of vaccination, route of administration, facility where vaccine was administered, dose, manufacturer, and lot number.

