## 4.2 COVID-19 at KPSC

At KPSC, diagnostic testing for SARS-CoV-2 is offered free of charge with an order from a KPSC physician, which can be requested by email, in person or through a virtual visit. Prioritization for testing has evolved during the pandemic, with an initial emphasis on individuals with symptoms (particularly high-risk groups) and prior to hospital admissions or certain outpatient procedures, with gradual expansion in 2020 to members without COVID-19 associated symptoms.

Testing in 2020 was primarily conducted by RT-PCR of nasopharyngeal/oropharyngeal swabs using the Roche cobas® SARS-CoV-2 assay on the Roche cobas® 6800 and 8800 analyzers or nasal/oropharyngeal swabs using the Aptima® SARS-CoV-2 assay on the Hologic Panther® analyzers. A small number of Abbott ID NOW™ COVID-19 rapid tests were conducted in limited settings (e.g., obstetrics, pulmonary medicine, and infectious disease departments); these were phased out by end of 2020. In November 2020, KPSC opened a new regional COVID-19

laboratory with Thermo Fisher Scientific Amplitude Solution instruments and also added saliva testing for asymptomatic individuals, increasing testing capacity to approximately 52,000 tests per day. In January 2021, voluntary weekly saliva testing was introduced for physicians and employees working in patient-facing areas.

As of July 2021, the TaqPath™ COVID-19 High-Throughput Combo Kit on the Thermo Fisher Scientific Amplitude Solution is used for the majority of SARS-CoV-2 molecular tests. A small proportion of tests are conducted using the Roche cobas® SARS-CoV-2 assay on the Roche cobas® 8800 System or the Roche cobas® SARS-CoV-2 & Influenza A/B assay on the Roche cobas® Liat® System; these tests can be ordered in limited circumstances when a provider requires an expedited result. The Aptima® SARS-CoV-2 assay on the Hologic Panther® System was phased out in early 2021.

Table 2. SARS-CoV-2 molecular tests and diagnoses among members of Kaiser Permanente Southern California during 01/01/2020-12/31/2020

|                                                                                 | Age (years) |         |         | Total     |
|---------------------------------------------------------------------------------|-------------|---------|---------|-----------|
|                                                                                 | 12-17       | 18-64   | ≥65     |           |

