| Number of patients tested for SARS-CoV-2 with RT-PCR test                       | 48,290      | 825,670 | 184,197 | 1,058,157 |
| Number of patients with a positive SARS-CoV-2 RT-PCR test                       | 13,788      | 200,403 | 24,452  | 238,643   |
| Number of patients with a COVID-19 diagnosis                        | 15,807      | 247,628 | 31,960  | 295,395   |
| Number of patients admitted to hospital with a COVID-19 diagnosis   | 87          | 10,871  | 7,980   | 18,938    |
| Number of patients admitted to ICU with a COVID-19 diagnosis        | 13          | 2,928   | 2,227   | 5,168     |
| Number of deaths within 31 days after the first COVID-19 diagnosis  | 1           | 715     | 2,038   | 2,754     |

A COVID-19 diagnosis includes those with a positive SARS-CoV-2 RT-PCR test result or a COVID-19 diagnosis code only.

As of December 31, 2020, over 1 million SARS-CoV-2 RT-PCR tests had been performed at KPSC, of which 17.4% were among individuals aged ≥65 years and 4.6% were among adolescents aged 12-17 years (Table 2). There were 238,643 members testing positive (13,788 members aged 12-17 years and 24,452 members aged ≥65 years). Additional members were diagnosed with COVID-19 based on positive test results outside of KPSC or clinical presentation and contact history, for a total of 56,752 members with a COVID-19 clinical diagnosis only. Approximately 25.0% (7,980/31,960) of COVID-19 patients aged ≥65 years were hospitalized, compared to only 4.4% (10,871/247,628) who were hospitalized among patients aged 18-64 years and 0.6% (87/15,807) who were hospitalized among patients aged 12-17 years. The proportion of COVID-19 patients being admitted to the ICU was 7.0% in patients aged ≥65 years versus 1.2% in patients aged 18-64 years. The proportion of COVID-19 patients who died within 31 days after a COVID-19 diagnosis or a positive test was 6.4% in patients aged ≥65 years versus 0.29% in patients aged 18-64 years.

As of July 2021, asymptomatic individuals who receive a COVID-19 test at KPSC may include individuals without COVID-19 symptoms who require or request testing. Both vaccinated and unvaccinated individuals are required to be tested for SARS-CoV-2 prior to KPSC procedures or admission. In addition, asymptomatic individuals can request testing (regardless of vaccination status) for any of the following reasons: travel, exposure to or close contact with a COVID-19-

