### 7.2 Outcome Definitions

The primary outcomes for this study are:

1. COVID-19 diagnosis will be defined as a SARS-CoV-2 positive molecular test or a COVID-19 diagnosis code (Primary Objective 1, Secondary Objectives 1-12, 14)
2. Severe COVID-19 disease includes COVID-19 hospitalization (hospitalization with a SARS-CoV-2 positive test or a COVID-19 diagnosis, or a hospitalization occurring  $\leq 7$  days after a SARS-CoV-2 positive test, with chart review to confirm severe COVID-19 symptoms) and COVID-19 mortality (death during COVID-19 hospitalization) (Primary Objective 2, Secondary Objectives 13, 15)

We will ascertain the first occurrence of COVID-19 diagnosis or severe COVID-19 disease  $\geq 14$  days after the index date.

Incident COVID-19 cases (identified through diagnosis code or positive molecular test) will be separated into symptomatic and asymptomatic COVID-19 cases. COVID-19 symptoms will be identified using a natural language processing (NLP) algorithm (currently being submitted for publication). The NLP algorithm will be applied to clinical notes before and after the incident COVID-19 diagnosis date to search for COVID-19 related symptoms. COVID-19 cases with no symptoms identified will be considered asymptomatic cases.

Positive SARS-CoV-2 tests conducted for surveillance of asymptomatic individuals will also be used as a preliminary approach to identify asymptomatic COVID-19 cases until the NLP algorithm is finalized. The use of testing data in asymptomatic individuals will facilitate assessment of VE against asymptomatic COVID-19 for the first interim analysis, whereas the

more comprehensive NLP approach will require more time to apply and will be used for subsequent analyses.

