## 10 Statistical Analysis Plan for Vaccine Effectiveness Against SARS-CoV-2 Variants (Study Objectives 16-17)

As multiple SARS-CoV-2 variants of concern (VOCs) and variants of interest (VOIs) have been identified over the course of the pandemic, it is essential to identify the viral variant causing disease in this long-term effectiveness study. WGS of SARS-CoV-2 positive specimens from vaccinated and unvaccinated individuals will be performed to achieve the following secondary objectives:

16. Assess the VE of two doses of Moderna COVID-19 vaccine against SARS-CoV-2 variants (using both test-negative and cohort designs)
17. Assess the VE of one dose of Moderna COVID-19 vaccine against SARS-CoV-2 variants (test-negative design only)

To assess VE of 2 doses and 1 dose of Moderna COVID-19 vaccine against SARS-CoV-2 VOCs and VOIs (Secondary Objectives 16 and 17), we aim to use a test-negative design (TND). The TND includes all sequencing data and more easily facilitates both 2-dose and 1-dose VE analyses. In contrast, a cohort design includes all vaccinated individuals; however, the cohort analysis will only be conducted for the final analysis if the proportions of positive SARS-CoV-2 tests at KPSC and positive specimens sent for sequencing among COVID-19 cases (i.e., COVID-19 diagnosis outcome) are similar between vaccinated and unvaccinated groups; if the proportions are substantially different a cohort design will yield biased results. The threshold for testing individuals with symptoms suggestive of COVID-19 at KPSC does not differ by vaccination status. VOCs and VOIs will be selected for analyses based on prevalence in the KPSC population and scientific interest. Descriptive analyses will include the percentages of specimens from vaccinated and unvaccinated individuals sequenced with valid results, stratifying by cycle threshold (Ct) values, specimen type, and symptomatic/asymptomatic test types. We will also examine the proportions of vaccinated and unvaccinated individuals with each VOC and VOI overall, by specific characteristics (e.g., age, sex, race/ethnicity, immunocompromised status, other comorbidities, history of COVID-19), COVID-19 hospitalization/hospitalized death, and month of specimen collection.

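### Section 7.2 counts a case as asymptomatic when NLP finds no symptom, without requiring that a clinical note exists, so VE against asymptomatic COVID-19 (Secondary Objective 10) may be biased

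*Protocol*

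**What the plan says.** Section 7.2 applies the symptom split to every incident case: "Incident COVID-19 cases (identified through diagnosis code or positive molecular test) will be separated into symptomatic and asymptomatic COVID-19 cases". The NLP approach has one source of information: "The NLP algorithm will be applied to clinical notes before and after the incident COVID-19 diagnosis date to search for COVID-19 related symptoms". The default follows: "COVID-19 cases with no symptoms identified will be considered asymptomatic cases". The section gives no window length, no minimum number of notes and no category for unknown status.

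For the first interim analysis, sections 7.2 and 8.4 identify asymptomatic cases from positive surveillance or asymptomatic tests instead. NLP takes over in later analyses. Section 8.4 places secondary analyses at the fourth interim and the final analysis. The early exceptions include asymptomatic COVID-19 only at the first interim; the second interim adds only pregnancy. The NLP default therefore governs two analyses of Objective 10.

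Three other places bear on documentation:
- Section 4.2, on test orders: "which can be requested by email, in person or through a virtual visit".
- Section 4, on outside care: "Care received outside the KPSC system is captured through claims".
- Section 4.2, on cases beyond the KPSC test positives: "Additional members were diagnosed with COVID-19 based on positive test results outside of KPSC or clinical presentation and contact history". It counts 56,752 such people in 2020.

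Section 10 shows that a symptom-related test label is already held, since the sequencing descriptives are planned "stratifying by cycle threshold (Ct) values, specimen type, and symptomatic/asymptomatic test types".

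**The concern.** The rule treats a note that records no symptoms and the absence of any note as the same finding. A symptomatic person whose record holds no searchable text becomes an asymptomatic case. These are true infections placed in the wrong class, not false events.

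Objective 10 then estimates a mixture of VE against asymptomatic infection and VE against undocumented symptomatic infection, and Objective 11 loses the same cases. A larger cohort would narrow the interval without removing the problem.

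No safeguard appears elsewhere. Section 8.4 analyses Objective 10 in the same way as the primary analysis. Section 13 discusses outcome misclassification through test capture, test sensitivity and failed sequencing, but not through symptom status. By contrast, Objective 8 requires chart-confirmed symptoms before a diagnosis code alone counts as a reinfection, and Table 3 gives smoking and BMI an unknown category.

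**Working it through.** **1. The one relevant figure in the protocol.** From Table 2, 295,395 diagnoses − 238,643 RT-PCR positives = 56,752, which matches section 4.2. As a share, 56,752 / 295,395 = 19.2%. These are cases with a clinical diagnosis only in 2020. This is not the share without notes: some of these cases will have notes, and some test-positive cases will not. It shows only that the group whose documentation cannot be taken for granted is not small.

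**2. Model.** All inputs below are assumptions, because the protocol gives none of them.
- a = share of infections in the unvaccinated that are truly asymptomatic: 0.2 to 0.4
- VEa, VEs = true VE against asymptomatic and symptomatic disease: 70% and 90%, or 50% and 80%
- m_u, m_v = share of symptomatic cases with no readable note in the unvaccinated and the vaccinated: 0.1 to 0.2

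Reported asymptomatic HR = [(1 − VEa)·a + (1 − VEs)·(1 − a)·m_v] / [a + (1 − a)·m_u]

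**3. Equal missingness, VEa 70%, VEs 90%.**
- a = 0.4, m = 0.1: (0.3×0.4 + 0.1×0.6×0.1) / (0.4 + 0.6×0.1) = 0.126 / 0.46 = 0.274, so VE = 72.6%
- a = 0.2, m = 0.2: (0.3×0.2 + 0.1×0.8×0.2) / (0.2 + 0.8×0.2) = 0.076 / 0.36 = 0.211, so VE = 78.9%

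The share of unvaccinated asymptomatic cases that are in truth symptomatic is 0.06 / 0.46 = 13% in the first case and 0.16 / 0.36 = 44% in the second.

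**4. Other scenarios.** Ranges are over a = 0.2 to 0.4.

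| True VEa / VEs | m_u | m_v | Reported VEa |
|---|---|---|---|
| 70% / 90% | 0.2 | 0.1 | 75.8-81.1% |
| 70% / 90% | 0.1 | 0.2 | 71.3-72.9% |
| 50% / 80% | equal, 0.1-0.2 | equal, 0.1-0.2 | 53.9-63.3% |
| 50% / 80% | 0.2 | 0.1 | up to 67.8% |

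**5. When the error vanishes or reverses.** Reported VE falls below true VE only if (1 − VEs)·m_v > (1 − VEa)·m_u, that is, if m_v / m_u > (1 − VEa) / (1 − VEs). The threshold is 0.3 / 0.1 = 3 for 70%/90% and 0.5 / 0.2 = 2.5 for 50%/80%. If VEa = VEs and m_u = m_v, there is no bias. If VEa = VEs and missingness differs, the error can go either way: with both VEs at 90% and missingness of 19.2% in one arm and 10% in the other, reported VEa is 87-92%.

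**6. Objective 11.** Reported symptomatic HR = (1 − VEs)·(1 − m_v) / (1 − m_u). With equal missingness, VEs is unchanged. With m_u = 0.2 and m_v = 0.1, 0.1×0.9 / 0.8 = 0.1125, so 90% becomes 88.8%. With the arms reversed, 0.1×0.8 / 0.9 = 0.0889, so it becomes 91.1%.

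**The case against.** The strongest reply is that section 7.2 is an outline. Note types, search window and sparse records may be settled in the NLP algorithm's own description or in the separate Data Management and Statistical Analysis Plan listed in Table 6, neither of which is at hand. This stands for the window and the note types. It does not stand for the default, which the protocol states without condition: followed as written, a case with no note is asymptomatic.

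A second reply is that the routes to a missing note are inferences. This is right.
- Section 4.2 still requires a KPSC physician's order and does not say whether an email request leaves searchable text.
- Section 4 does not say that outside care comes without notes.
- The search covers notes before and after diagnosis, so later KPSC contacts may supply symptoms.

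Cases without notes are therefore plausible, but not shown.

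A reader might go further and infer that a patient admitted elsewhere would be labelled asymptomatic. The protocol does not support that. Section 7.2 requires chart review to confirm severe symptoms in certain hospitalised cases and does not limit this to KPSC admissions, although it does not link that review to the symptom split either.

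A third reply is that the shift may be small. At the low end of the equal-missingness range it is 2.6 points, and Objective 10 is secondary. This also stands and limits the weight of the point.

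**Conclusion.** The default in section 7.2 should be changed before the fourth interim analysis. Under it, VE against asymptomatic COVID-19 may be biased. If missingness is similar by arm, the estimate is pulled toward the symptomatic VE: a true 70% is reported as 72.6-78.9% under the assumed 10-20% missing notes, 20-40% asymptomatic share and symptomatic VE of 90%.

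Three stronger readings are tempting but unsupported.
- That VE is biased by a known amount: every model input is assumed, and there is no bias if both the VEs and the missingness are equal.
- That the error is as likely to be downward as upward: every figure computed for the 70%/90% and 50%/80% examples lies above the true value, and understatement in the 70%/90% example needs vaccinated cases to lack notes more than three times as often.
- That every analysis from the second interim on is affected: only the fourth interim and final analyses of Objective 10, and the matching analyses of Objective 11, use the NLP split.

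The primary objectives do not use symptom status, and the first interim Objective 10 analysis uses test type.

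**What to change.** In section 7.2, replace the default with three steps:
1. Class a case as asymptomatic by NLP only if at least one clinical note exists in a fixed window around the diagnosis date and the notes there record no COVID-19 symptom.
2. If there is no note, use the recorded symptomatic or asymptomatic test type.
3. If that is also missing, class the case as symptom status unknown.

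Report the number of unknowns by vaccination status. Present Objectives 10 and 11 with unknowns censored at diagnosis, together with two bounding analyses that assign all unknowns to the asymptomatic class and then all to the symptomatic class.

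The cost is one definition, modest programming on data already held, and somewhat fewer classified events. There is also a statistical cost. People found by screening, who are often truly asymptomatic, may be the least likely to have notes. Test type recovers those tested at KPSC, but code-only cases may have no KPSC test type. The censored analysis is unbiased only if unknown status is unrelated to symptoms within each arm. The bounds and the counts by arm should therefore carry the conclusion, not the censored estimate alone.

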### 7.3 Other Variable Definitions

Other variables (Table 3) will be identified from EHR and considered in analyses when feasible and appropriate as covariates or stratification variables.

Table 3. List of possible covariates

|                                                                                                  | Categories                                                                                |
|--------------------------------------------------------------------------------------------------|-------------------------------------------------------------------------------------------|
| Variables to be assessed at index date (Day 0)                                            |                                                                                           |
| Age at index date, years                                                                         | 12-17, 18-44, 45-64, 65-74, 75+                                                           |
| Sex                                                                                              | Female, Male                                                                              |
| Race/Ethnicity                                                                                   | Non-Hispanic White, Non-Hispanic Black, Non-Hispanic Asian, Hispanic, Other/Unknown       |
| Month of index date                                                                              | By calendar month                                                                         |
| Socioeconomic status                                                                      |                                                                                           |
| Medicaid                                                                                         | Yes, No                                                                                   |
| Neighborhood median household income                                                             | To be determined based on variable distribution                                           |
| Medical center area                                                                              | MC1, MC2, MC3, ...                                                                        |
| Pregnancy status                                                                                 | Yes (1 st trimester, 2 nd trimester, 3 rd trimester), No |
| Variables to be assessed in the two years prior to index date (-730 to -1 day, inclusive) |                                                                                           |
| Any smoking behavior                                                                             | Yes, No, Unknown                                                                          |
| Most recent Body Mass Index (BMI) measurement                                                    | <18.5, 18.5 - <25, 25 - <30, ≥30 - <35, 35 - <40, 40 - <45, ≥45, Unknown                  |
| Variables to be assessed in the year prior to index date (-365 to -1 day, inclusive)      |                                                                                           |
| Charlson comorbidity score [14]*                                                                 | 0, 1, 2+                                                                                  |
| Autoimmune conditions                                                                     |                                                                                           |
| Rheumatoid arthritis                                                                             | Yes, No                                                                                   |
| Inflammatory bowel disease                                                                       | Yes, No                                                                                   |
| Psoriasis                                                                                        | Yes, No                                                                                   |
| Psoriatic arthritis                                                                              | Yes, No                                                                                   |
| Multiple sclerosis                                                                               | Yes, No                                                                                   |
| Systemic lupus erythematosus                                                                     | Yes, No                                                                                   |
| Health care utilization                                                                   |                                                                                           |
| Number of virtual and outpatient encounters                                                      | 0, 1-4, 5-10, 11+                                                                         |
| Number of emergency encounters                                                                   | 0, 1, 2+                                                                                  |
| Number of inpatient encounters                                                                   | 0, 1, 2+                                                                                  |
| Preventive care - with other vaccinations, screenings, and well-visits from all settings         | Yes, No                                                                                   |

|                                                                                                                    | Categories                          |
|--------------------------------------------------------------------------------------------------------------------|-------------------------------------|
| Chronic diseases                                                                                            |                                     |
| Kidney disease                                                                                                     | Yes, No                             |
| Heart disease                                                                                                      | Yes, No                             |
| Lung disease                                                                                                       | Yes, No                             |
| Liver disease                                                                                                      | Yes, No                             |
| Diabetes                                                                                                           | Yes, No                             |
| Other variables                                                                                             |                                     |
| KPSC physician/employee status at index date                                                                       | Yes, No                             |
| Frailty index in year prior to index date (-365 to -1 day, inclusive), using method by Kim et al. [15]             | To be determined based on quartiles |
| History of COVID-19 diagnosis (from March 1, 2020 to index date, inclusive)                                        | Yes, No                             |
| History of SARS-CoV-2 molecular test performed (from March 1, 2020 to index date, inclusive), regardless of result | Yes, No                             |
| Concomitant vaccine                                                                                                | Yes, No                             |
| Immunocompromised status                                                                                    | Yes, No                             |
| HIV/AIDS any time prior to index date                                                                              | Yes, No                             |
| Leukemia, lymphoma, congenital immunodeficiencies, asplenia/hyposplenism any time prior to index date              | Yes, No                             |
| Organ transplant any time prior to index date                                                                      | Yes, No                             |
| Immunosuppressant medications at index date                                                                        | Yes, No                             |

\* Charlson comorbidities include myocardial infarction, congestive heart failure, peripheral vascular disease, cerebrovascular disease, connective tissue disease, dementia, chronic pulmonary disease, connective tissue disease, peptic ulcer disease, diabetes mellitus, paraplegia and hemiplegia, renal disease, liver disease, cancer, metastatic solid tumor, human immunodeficiency virus (HIV), and acquired immunodeficiency syndrome (AIDS)

The covariates included in adjusted analyses will be determined by scientific relevance, association with exposure, and data availability. Specifically, we will select covariates by following these steps:

1. The distribution of covariates will be reviewed. Some categories of a categorical variable with small sample sizes may be redefined or combined into one category.
2. The association of baseline covariates with exposure will be assessed. We will use standardized difference to assess the balance of covariates between exposed and unexposed cohorts. Unlike p-values, for which magnitude is highly related to sample size, standardized difference is a unified approach to quantifying the magnitude of difference between groups regardless of sample size, where an absolute value less than 0.1 is considered a negligible difference. Potential confounders will be determined by absolute standardized difference (ASD) >0.1.
3. All potential confounders from Step 2 will be included in the analyses. Steps 1 and 2 will be repeated for the 2-dose cohort and the 1-dose cohort. Matching variables (age, sex, race/ethnicity and index date), which are considered important risk factors, will be kept in the

adjusted model for possible imbalance on matching variables due to loss to follow-up or subgroup analysis (e.g., by baseline comorbidities).

